### 2.12. Secondary outcome measurement

The secondary outcomes include the changes in the movement of the eyebrow and lip, symptoms related to or accompanied by FP, FDI, EQ-5D-5L, EQ-VAS, and the results of EMG, ENoG and Blink Reflex test, as well as the safety and feasibility analyses.

The movement of the eyebrow and lip will be measured at the top of the eyebrow and the corner of the mouth from each side, and the lengths will be compared.

Symptoms related to FP, including fatigue or overwork, poor sleep, stress, indigestion, loss of appetite, and aversion to cold or wind, will be examined on a checklist. Additionally, symptoms accompanied by FP, including postauricular pain, increase in tear, dry eye, ear fullness, hyperacusis, taste disorder, paresthesia of the tongue, and vesicle, will be evaluated using a 3-point Likert scale.

FDI is a disease-specific, self-report instrument for the assessment of disabilities of patients with facial nerve disorders, including physical function and social/well-being function. It has been proven that FDI subscales produce reliable measurements, with construct validity for measuring patient-focused disability of individuals with disorders of the facial motor system.^[12]^

The EQ-5D is a generic instrument for describing and valuing health based on a descriptive system, which defines health in terms of 5 dimensions: mobility, self-care, usual activities, pain/discomfort, and anxiety/depression.^[13]^ The EQ-5D-5L includes 5 levels of severity in each of the existing 5 EQ-5D dimensions,^[14]^ which provides precise and sensitive measurements of health status.^[15]^ The EQ-VAS is a vertical, calibrated line, bounded at 0 “worst imaginable health state” and 100 “best imaginable health state,”^[16]^ which exhibits sufficient construct validity.^[17]^

The EMG, ENoG, and Blink Reflex test are useful indicators for predicting recovery and defective healing with high prognostic value. It is known that the timing of electrophysiologic tests is important in order to predict the prognosis accurately.^[18]^ It takes about 72 hours for Wallerian degeneration to propagate from intratemporal part, which is the damaged part, to stylomastoid foramen, which is the distal part electrically stimulated during electrophysiologic tests.^[19]^ Reliable prognostic information is obtainable after 10–14 days from the onset of PFP.^[20]^ Electrophysiologic tests will be conducted 2–3 weeks from the onset at the Department of Physical Medicine of Rehabilitation in Kyung Hee University Hospital.

The safety analysis will be conducted by estimating the number of participants with and without serious adverse events (SAEs) during the study. If adverse event occurs, the investigators will record it in detail in the case report form. If participants complain of side effects or abnormal reactions, or if the progress of the study threatens the safety of the participants, the investigators may decide to suspend or prematurely terminate the study for those participants, and report these to Institutional Review Board.

The WIWI questionnaire is a 5-item tool used to evaluate the feasibility of a clinical study and explores the patient’s experience of an intervention.^[21]^ With reference to previous research,^[21]^ it is meaningful to conduct the questionnaire after the participants receive Korean medicine treatment. The participants will fill in the WIWI questionnaire at the end of the study, and the results will be analyzed to assess the feasibility of Korean medicine treatments.

### 2.13. Statistical analysis

For the primary outcome measure, including the H-B grading system, the proportion, and ratio of patients with H-B grade 2 or lower after the treatments will be analyzed.^[22,23]^

For the secondary outcome measures, including the movement of the eyebrow and lip, symptoms related to or accompanied by FP, FDI, EQ-5D-5L, EQ-VAS, WIWI questionnaire, and the results of EMG, ENoG, and Blink Reflex test, data will be analyzed using the mixed-effect model repeated measure, with visit time as a fixed factor and subject as a random factor.

Prognosis will be estimated using the results of EMG, ENoG and Blink Reflex test, and the correlation between the prognosis and the changes in H-B grade, movement of the eye and lip, symptoms related to or accompanied by FP, or the types of Korean medicine treatments provided will be analyzed using logistic regression analysis, considering age and sex as a potential confounders.

Since various Korean medicine treatments will be used, all treatments provided to the subjects will be recorded, and adverse events will be evaluated at every visit. For the safety analysis, the number of participants with and without SAEs will be estimated. The degree of symptoms and relevance to treatments will be analyzed, and SAE details will be described.

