## 2. Methods

### 2.1. Study design

This is a multicenter, prospective, observational study on Korean medicine treatment based on the CPGs in patients with acute PFP. PFP is diagnosed after excluding central facial palsy through symptoms and history taking. The participants will be recruited from 1 Korean medicine hospital and 8 Korean medicine clinics, from August 2021 to February 2022. To minimize selective bias, patients with facial palsy who visited the relevant medical institution are sequentially recruited and screened. The participants will receive Korean medicine treatments at each hospital or clinic, and fill in survey questionnaires from the baseline until six weeks later. The participants’ survey questionnaires include symptoms related to or accompanied by FP, Facial Disability Index (FDI), EuroQol 5-dimension 5-level (EQ-5D-5L), EuroQol Visual Analogue Scale (EQ-VAS), and Was It Worth It (WIWI) questionnaire. The participants will undergo electromyography (EMG), electroneurography (ENoG), and Blink Reflex test between visits 3 and 4, which is 2–3 weeks from the onset of PFP. The changes in House-Brackmann (H-B) grade and movement of the eyebrow and lip will be evaluated by investigators, and the treatments provided to the participants and adverse events will be recorded.

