### 2.7. Treatment

The participants will receive Korean medicine treatments based on the CPGs but will not receive any intentional treatments. The Korean medicine treatments may include acupuncture, electroacupuncture, pharmacopuncture, moxibustion, herbal medicine, and cupping. The investigators will keep a record of the treatments provided to the participants.

According to the CPGs,^[6]^ acupoints such as ST4, ST6, EX-HN5, TE17, GB14, SI18, LI4, and GB20 are frequently used for acupuncture treatment for FP, and other acupoints can also be used according to the patient’s symptoms and judgment of Korean medicine doctors. In addition, electrical stimulation can be applied to the acupoints. In case of herbal medicine treatment, Korean medicine doctors determine the prescription according to the condition and characteristics of each patient. Acupoints such as TE17 and GB12 can be used for wet cupping. Pharmacopuncture such as Bee venom and placenta, and moxibustion treatment can be applied on face and behind the ear.

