### 2.9. Investigator assessment

The investigators, who are Korean medicine doctors working in the hospital and clinics participating in this study, will assess the changes in H-B grade and movement of the eyebrow and lip. All measurements and assessments will be performed at baseline and once a week until 6 weeks later.

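### The treatment-type regression names only age and sex as confounders in a non-randomised study, so baseline severity can distort the association; visit-1 H-B grade is already collected and should be added

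*Protocol article*

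**What the plan says.** Section 2.13 estimates prognosis from EMG, ENoG and the blink reflex. It then relates prognosis to change in H-B grade, eye and lip movement and symptoms, "or the types of Korean medicine treatments provided will be analyzed using logistic regression analysis, considering age and sex as a potential confounders". The article names no other adjustment variable for this analysis.

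Section 2.1 describes a multicentre, prospective, observational study: "The participants will be recruited from 1 Korean medicine hospital and 8 Korean medicine clinics". Section 2.7 leaves the treatment mix open: "The Korean medicine treatments may include acupuncture, electroacupuncture, pharmacopuncture, moxibustion, herbal medicine, and cupping". Within that menu, two choices are tied to the patient. For herbal medicine, "Korean medicine doctors determine the prescription according to the condition and characteristics of each patient". For acupuncture, beyond the commonly used points, "other acupoints can also be used according to the patient’s symptoms and judgment of Korean medicine doctors".

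Table 1 schedules the H-B grade at visit 1 and at every later visit, and section 2.9 confirms a baseline assessment. Baseline severity is therefore on file for each participant.

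**The concern.** When doctors choose treatment and the patient's condition informs that choice, patients given a modality may differ in severity from those not given it. Severity is also what electrophysiologic prognosis reflects. A model without severity then credits the modality with a difference that was there at entry. This is confounding by indication. Age and sex are not measures of severity and cannot stand in for it.

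By naming confounders, section 2.13 shows that it means to control confounding, but the set it names omits the most obvious candidate. The Conclusion of the abstract and section 3 say that the study is meant to help complement and improve the guideline. A reader of the results could take a treatment-type association as information about a modality when it only shows who received it.

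**Working it through.** **Number of analysable patients.** Section 2.4 assumes 80% with H-B grade 2 or lower, ±10 points, P = .05 and 15% dropout.

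- 1.96² × 0.8 × 0.2 / 0.10² = 61.5, rounded up to 62.
- 62 / 0.85 = 72.9, rounded up to 73, which is the stated total.

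So n = 62 is used below.

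**Assumptions, since the article gives no figures.** Half the patients are severe. Poor prognosis occurs in 40% of severe and 10% of milder patients. The modality has no effect. It is given to a share *a* of severe patients and 1 − *a* of milder patients, so half of all patients receive it, and a share *a* of those who do are severe.

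**Formula.**

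- Poor prognosis if treated: a × 0.4 + (1 − a) × 0.1
- Poor prognosis if untreated: (1 − a) × 0.4 + a × 0.1
- Apparent odds ratio: ratio of the two odds. The true value is 1.

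| Given to severe / milder | Poor if treated | Poor if untreated | Apparent OR |
|---|---|---|---|
| 50 / 50 | 0.25 | 0.25 | 1.00 |
| 60 / 40 | 0.28 | 0.22 | (0.28/0.72)/(0.22/0.78) = 1.38 |
| 70 / 30 | 0.31 | 0.19 | (0.31/0.69)/(0.19/0.81) = 1.92 |

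**False-positive rate at n = 62**, from 2,000 simulated logistic fits per row:

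| Given to severe / milder | Age and sex only | Severity added |
|---|---|---|
| 50 / 50 | 4.1% | 4.3% |
| 60 / 40 | 7.2% (8% in a separate run) | 4.5% |
| 70 / 30 | 17.0% (17% and 17.5% in separate runs) | 4.8% |

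A hand check at 70/30 with 31 patients per group agrees roughly. The standard error of the log odds ratio is √[1/(31 × 0.31 × 0.69) + 1/(31 × 0.19 × 0.81)] = 0.60. Then ln 1.92 / 0.60 = 1.08, which gives a rejection rate of about 19% at the two-sided 5% level.

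**Check with another outcome.** Section 2.13 does not say which variable is dependent. With recovery as the outcome (80% recovered, half severe, no treatment effect), the age- and sex-adjusted odds ratio for treatment is:

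- 0.89 when severity doubles both the odds of treatment and the odds of non-recovery;
- 0.71 at odds ratios of 3 and 4;
- 0.59 at odds ratios of 4 and 6.

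Adding severity brings it back to about 1.0 each time. False-positive rates are 6.7% (3 and 4) and 10.1% (4 and 6), against 4.9% and 4.3% with severity added. If severity does not drive treatment, the odds ratio is 0.99-1.00.

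**Room in the model.** Under the first set of assumptions, 25% have poor prognosis: 62 × 0.25 = 15.5 events.

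- Age, sex and one modality: 15.5 / 3 = 5.2 events per parameter.
- H-B grade added: 15.5 / 4 = 3.9.
- Diagnosis added as well: 15.5 / 5 = 3.1, before any site term.

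If 7% of patients had Ramsay Hunt syndrome (an assumption), the diagnosis term would be empty or perfectly separated in about 35% of samples of this size.

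**The case against.** **The text does not say that severity decides modality.** This stands. The sentence on condition and characteristics concerns which herbal prescription is given, and the one on symptoms concerns extra acupoints. A reader might infer that section 2.7 allocates electroacupuncture, cupping, moxibustion or pharmacopuncture by severity, but it does not. A reader might also infer that the nine sites have different treatment habits. The article says only that each site treats its own patients, and that treatment follows the guideline. Both inferences are reasonable, and both remain inferences.

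**The bias may be small or absent.** This stands too. False-positive rates well above 17% need stronger assumptions. At 80/20 allocation the odds ratio is 2.70 and simulated rates are 33-36%, but that requires a severity-to-treatment odds ratio of (0.8/0.2)/(0.2/0.8) = 16. Nothing in the article supports that figure. The bias can arise; the documents do not show that it will.

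**The analysis is a secondary correlation.** It is, and nothing says that a modality would be regraded in the guideline on this result alone. However, the section speaks of confounders and does not limit the treatment-type result to description.

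**A fuller covariate list may exist elsewhere.** The article does not say that age and sex are the only covariates. But it goes beyond leaving the matter open and names a set, and that set lacks severity.

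**The data are too sparse for a wide adjustment.** This stands and limits the remedy. It argues for spending the one extra parameter on baseline severity.

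**Conclusion.** The concern holds as a moderate point about a secondary analysis. The named adjustment set is too narrow for a non-randomised comparison of treatment types in which at least part of the treatment follows the patient's condition.

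Under the assumptions shown, a null modality would show an odds ratio of 1.4 to 1.9 and be declared associated in about 7-8% to 17% of studies at n = 62, instead of about 5%. If severity does not influence which modality is given, there is no bias. Size and direction therefore depend on allocation patterns that the article does not describe.

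The primary analysis, the proportion with H-B grade 2 or lower, is not touched.

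**What to change.** In section 2.13, add visit-1 H-B grade to age and sex in the treatment-type models, as a single ordinal or linear term. State that the treatment-type results are exploratory associations and do not estimate the effect of a modality.

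Examine diagnosis (Ramsay Hunt syndrome versus other) and hospital versus clinic only as sensitivity analyses, if the event count allows, with penalised estimation if needed. A full set of site terms is unlikely to be supported.

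The cost is a sentence or two of text, no new data, one more parameter and slightly wider intervals. Adjustment will reduce confounding but not remove it. The simulations assume that severity is captured exactly, whereas patients enter within 7 days of onset and the Introduction says that signs typically peak in the first week, so some visit-1 grades may precede the peak. This is a further reason for the non-causal label.

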### 2.4. Sample size

Based on similar studies, the clinical experiences of the investigators, and the preliminary research results,^[7,8]^ the sample size was determined. In this study, the therapeutic effect is defined as H-B grade 2 or lower. Assuming that the ratio of the patients with H-B grade 2 or lower after the treatments for 6 weeks is 80% (±10%, *P* = .05), considering the power of 80% and dropout rate of 15%, a total of 73 participants will be required. There were 2708 patients with PFP from 2006 to 2015 in Korea, and the average incidence rate over 10 years was 25.9 cases per 100,000 people.^[9]^ Therefore, the calculated 73 study subjects can be sufficiently recruited for the study period of about 6 months.

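### The logistic regression in 2.13 names only age and sex as confounders and omits baseline severity, so its treatment-type associations are at risk of confounding; its outcome and structure are also not stated

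*Protocol article*

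**What the plan says.** All references are to the protocol article.

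- **Prognosis variable (2.13).** "Prognosis will be estimated using the results of EMG, ENoG and Blink Reflex test". Its correlation is then sought with change in H-B grade, movement, "symptoms related to or accompanied by FP, or the types of Korean medicine treatments provided".
- **Method and adjustment (2.13).** These relations "will be analyzed using logistic regression analysis, considering age and sex as a potential confounders". No other covariate is named. The section does not say which variable is dependent, or whether there is one model or several.
- **Treatment (2.7).** Treatments "may include acupuncture, electroacupuncture, pharmacopuncture, moxibustion, herbal medicine, and cupping", which makes six types. For herbal medicine, "Korean medicine doctors determine the prescription according to the condition and characteristics of each patient". Additional acupoints likewise depend on symptoms and the doctor's judgement.
- **Test timing (2.12).** "Electrophysiologic tests will be conducted 2–3 weeks from the onset". Section 2.1 places them between visits 3 and 4, and Table 1 marks visit 3.
- **Severity data.** Table 1 has H-B grade at visit 1 and every later visit, and a facial palsy history at screening. The eligibility criteria in 2.2 require the diagnosis and onset within 7 days, so both are known at entry.
- **Binary endpoint (2.4).** "the therapeutic effect is defined as H-B grade 2 or lower". Section 2.11 defines the primary outcome as H-B change from baseline to week 6.

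**The concern.** The study has no control group and treatment is tailored to the patient. Severity at entry is the obvious common cause of what a patient receives, what the electrophysiologic tests show and how far the face recovers. Age and sex do not stand in for it. A treatment with no effect could look harmful if more severe cases tend to receive it, or helpful if milder cases do.

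There is also a timing problem. Relating a test at 2–3 weeks to H-B change counted from baseline credits the test with predicting change that had already happened.

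Finally, because the outcome and structure are open, a reader cannot tell how many events support each coefficient. One plausible reading leaves very few.

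This is a secondary analysis, and the primary proportion is unaffected. The article does present the study as a basis for improving the guideline, and treatment-type associations could be read as favouring one modality over another.

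**Working it through.** **1. The plan's sample size.** Inputs from 2.4: recovery 80%, ±10 points, 0.05 (taken as two-sided), dropout 15%.

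n = 1.96² × 0.80 × 0.20 / 0.10² = 61.5, rounded up to 62. Then 62 / 0.85 = 72.9, rounded up to 73, which is the stated total. So 62 completers is the plan's implied number.

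**2. Expected non-recoverers, if the outcome is H-B grade I–II at week 6.** Formula: 62 × (1 − recovery rate), divided by the number of parameters (intercept excluded).

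| Recovery | Non-recoverers | Per parameter, 3 parameters | Per parameter, 8 parameters |
|---|---|---|---|
| 70% | 18.6 | 6.2 | 2.3 |
| 80% | 12.4 | 4.1 | 1.55 |
| 90% | 6.2 | 2.1 | 0.8 |

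Three parameters are one predictor plus age and sex. Eight are six treatment types plus age and sex in one model. If all 73 complete, 80% recovery gives 73 × 0.20 = 14.6.

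**3. What this means for precision.** I simulated 1,000 data sets of 62 patients, with about 20% events, a binary predictor present in half the patients and a true log odds ratio of 0.70 (all but the 62 and 20% assumed). The estimates had mean 0.79 and SD 0.75 with three parameters, and mean 0.82 and SD 0.91 with eight. On the odds-ratio scale, a 95% range spans a factor of exp(1.96 × 0.75) = 4.3 either side with three parameters and exp(1.96 × 0.91) = 6.0 with eight.

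**4. If prognosis is the dependent variable.** The event count cannot be derived from the article. The smaller category cannot exceed 31 of 62, so the ceiling is 31/3 = 10.3 or 31/8 = 3.9 per parameter.

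**5. Size of confounding (illustration; inputs assumed).** Half the patients are severe. A treatment with no effect goes to 70% of severe and 30% of mild patients. A favourable result occurs in 60% of severe and 90% of mild patients, treated or not.

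- Treated: (0.35 × 0.60 + 0.15 × 0.90) / 0.50 = 0.345 / 0.50 = 69%.
- Untreated: (0.15 × 0.60 + 0.35 × 0.90) / 0.50 = 0.405 / 0.50 = 81%.
- Odds ratio: (0.69/0.31) / (0.81/0.19) = 0.52, although it is 1 within each severity group.

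The arithmetic is the same whether the favourable result is recovery or a good electrophysiologic finding.

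A simulation under other assumptions used a continuous severity score acting on both treatment and non-recovery. Adjusted for age and sex only, it gave a null treatment a median odds ratio for non-recovery of 1.3 (log odds ratio 0.5 per SD on each) to 2.3 (1.0 per SD). Between 4% and 18% of tests were significant. Adding severity returned the median to about 1.0.

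**6. Timing.** Visits 1 to 7 contain six visit-to-visit steps. The steps from visit 1 to 2 and from 2 to 3 end at or before the test. The Introduction says that signs usually peak in the first week and then ease, so change before the test is to be expected.

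**The case against.** The strongest reply is that the article does not set the model that a critic would most like to attack. Prognosis is one side of every pairing in 2.13. Treatment type is paired with electrophysiologic prognosis, not with week-6 recovery, and the items are joined by an *or* that allows separate small models. This stands. A reader might infer one joint regression of recovery on prognosis and all treatment types, with 12 events for eight or more parameters. The article does not say so, and the 1.6 per parameter holds only on that reading.

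Section 2.7 does not say that severity decides which of the six types is given. Its wording concerns the herbal prescription and the acupoints. This also stands, so severity-driven choice of type is a plausible inference and not a stated fact. But the mix is left to the doctor, and nothing in the plan breaks a link with severity.

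A high rate of chance findings across treatment types would not by itself show overfitting. Six independent tests at 5% give 1 − 0.95⁶ = 26.5% with at least one below 0.05 at any sample size.

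A fuller covariate list may exist in a document not shown. That is possible, but the article states a set, and the set leaves out severity.

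Electrophysiologic prognosis may partly represent severity. It can do so only where it sits in the same model, and it is measured after treatment has begun, so it does not replace baseline H-B grade.

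The test timing itself is justified in 2.12. The difficulty is relating the tests to change counted from baseline.

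**Conclusion.** The point holds as a risk, on either reading of the model. The named confounders omit baseline severity although it is recorded, so treatment-type associations are open to confounding that age and sex do not remove. Under the assumed inputs, a treatment with no effect shows an odds ratio for a favourable result of 0.52. The simulated range for non-recovery is 1.3 to 2.3. The true size depends on how strongly severity guides treatment, which the article does not give.

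H-B change from baseline includes change that preceded the tests.

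The dependent variable and model structure are not stated. If the outcome is H-B grade I–II at week 6, about 12 non-recoverers are expected (6 to 19), or about 4 per parameter in separate models and about 1.6 in a joint one.

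A reader might conclude that the results will be confounded and overfitted. The article does not support that certainty.

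**What to change.** Revise the regression paragraph in 2.13 as follows.

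1. State the dependent variable of each model, and that models are fitted separately.
2. **Treatment types:** one type per model, adjusted for baseline H-B grade as well as age and sex, with days from onset added as far as the event count allows. Label the results exploratory and non-causal.
3. **Prognosis:** relate the test result to H-B grade at visit 7, adjusted for H-B grade at the test visit. Visit 3 is the one marked in Table 1. The model then describes recovery after the test.
4. **Optional:** a penalised (Firth) logistic model, or a proportional-odds model on the H-B grades, would cope better with few events. Neither is required.

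The cost is a change of wording, since all variables are already collected or known at entry. The downside is fewer predictors per model and wider intervals. With grade II or lower as the outcome, treatment type, baseline grade (one linear term), age and sex make four parameters, or 12.4/4 = 3.1 non-recoverers each. Adding days from onset gives 12.4/5 = 2.5.
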